#### Mediators of change

Potential mediators that will be analyzed include (1) treatment fidelity as assessed by the therapist using an integrity questionnaire after each session. Therapists will document the interventions and treatment manuals that were used as well as the therapy homework the patient has to complete before the next session. (2) Additional potential mediators that will be analyzed are health-related quality of life, self-perception profiles, and emotion regulation strategies measured using the self-report KINDL^R^, Harter scale, and FEEL-KJ, respectively (see above). (3) Furthermore, treatment adherence assessed following each therapy session will be evaluated as a mediating factor using the Adherence Questionnaire (see above). This assessment will include four distinct items to define adherence, focusing on the patient’s engagement during the therapy sessions. Moreover, for each therapy-related homework task that the patient is given to complete before a session, execution adherence will be assessed after the session.

### Missing data

It is important to minimize treatment discontinuation among patients and ensure that all patients are followed up and documented after treatment discontinuation in order to collect the data according to the intention-to-treat (ITT) principle. Multiple imputation approaches will be employed to evaluate the potential impact of up to 20% attrition, considering proxy measures and assuming specific patterns of missingness not at random. These details will be documented in a statistical analysis plan. Additionally, supporting evidence will be provided by analyzing subjects who are essentially observed and treated per protocol.

## Oversight and monitoring

### Committees

This study is designed as a monocenter trial without external funding. Thus, there will be no external data monitoring or auditing committee. However, this will be considered for a subsequent larger trial.

### Harms

During each therapy session, therapists will inquire about potential adverse events, and participants will be encouraged to report any unexpected effects at any time during the study. All reported adverse events will be discussed with the PI in the regularly held supervision meetings. The principal investigator will be responsible for determining the necessary actions, including modifications to the protocol or, in extreme cases, terminating the trial.

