## Background

Anxiety and depressive disorders are highly prevalent during adolescence [1, 2], and the rates of these disorders have significantly increased as a consequence of the COVID-19 pandemic [3, 4]. They frequently co-occur and show a significant convergence of symptoms [5, 6]. Adolescents with anxiety or depressive disorders show lower social and academic functioning than unaffected peers [7, 8], and even more concerningly, have a higher risk of suicidality [9–11], which is a leading cause of death in young people [12]. The presence of affective disorders in adolescence and young adulthood further predicts poor health outcomes and functioning in adulthood [13, 14]. Considering the high prevalence and adverse impacts of these disorders, effective treatment for affected adolescents is crucial.

According to scientific consensus, cognitive-behavioural therapy (CBT) is the method of choice for treating anxiety and depressive disorders in both adults and youth (e.g., [15–17]). Nevertheless, a careful examination of the treatment effects of psychotherapy for depressed and anxious youth reveals only modest effect sizes. A significant proportion of affected youth are non-responders to therapy or continue to fulfill the criteria for a psychiatric diagnosis at the end of therapy [18–21]. Furthermore, findings regarding the long-term effects of CBT are mixed [15, 22].

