**Fig. 1 Fig1:**
[figure not shown]
Study design of the JAY trial

Following these sessions, patients will be randomly allocated to one of the two treatment arms. After randomization, a baseline phase will take place, followed by the T1 assessment. In the subsequent treatment phase, patients in both groups will receive state-of-the-art CBT. In the treatment group (CBT + JAY), homework and assessments will be conducted through the JAY app, while in the active control group (CBT), equivalent tasks will be completed on paper. Each treatment phase will consist of eight sessions with the patient and up to four sessions with a caregiver. The first treatment phase will be followed by the T2 assessment. The final main assessment (T3) will take place after the second treatment phase. Depending on the clinical significance of remaining internalizing symptoms, patients will then either continue with a third treatment phase, which will be followed by the T4 assessment, or the intervention will be stopped and they will proceed to a first follow-up assessment after 8 weeks (T4). A subsequent follow-up evaluation (T5) for all patients will be scheduled 6 months after T4.

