#### Adherence

Patients’ adherence to the study protocol will be ensured through the following measures: (i) During the patients’ weekly therapy sessions, adherence to the study protocol will be discussed alongside their regular progress reviews, including homework completion. Since the study data (e.g., homework completion rates, symptom tracking) are directly informative for the therapist’s clinical planning, this discussion naturally aligns with the therapeutic goals. (ii) Therapists will document adherence-related discussions and any protocol deviations in the Adherence Questionnaire, which will be regularly reviewed by the research team.

Treatment fidelity on the part of the therapists will be ensured through several measures: (i) Therapists will complete a structured protocol after each session, and (ii) a supervision session with the PI will be scheduled for every fourth therapy session.

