
### Participant timeline

The participant timeline and measurement schedule for the JAY trial will include four key stages: a screening process, a baseline phase, an intervention period, and a follow-up assessment. The screening process will assess whether families meet the study’s inclusion and exclusion criteria in several steps. First, families will be contacted by telephone for a brief standardized screening. If the initial criteria are met, the patient and a caregiver will be invited for an in-depth screening and information session. Participants who agree to join the study will complete initial questionnaires and undergo three diagnostic sessions to thoroughly assess eligibility (T0). This will be followed by randomization to the experimental or control group. After this, three sessions will be conducted to introduce the patient to their therapist, focusing on building a strong patient-therapist relationship and providing psychoeducation.

The screening process will be followed by a baseline phase that does not include any sessions with the study staff or therapist. Participants will use the JAY app [67] or paper-and-pencil sheets for the purpose of self-observation.

The pre-treatment assessment (T1) will mark the end of the baseline and beginning of the treatment phase. The first part of the treatment phase will involve eight sessions of cognitive-behavioural therapy and up to four sessions with caregivers, followed by an intermediate assessment (T2). The second part of the treatment phase will likewise consist of eight patient sessions and up to four caregiver sessions. Subsequently, another main assessment (T3) will follow. Non-responders to the treatment will be identified using the Internalizing scale from the YSR/11-18R [69] and will continue to receive CBT in a third part of the treatment phase. This will then be followed by a final assessment (T4). Responders to the treatment, as indicated by a lack of significant internalizing symptoms at the main assessment (T3), will conclude their participation in the study. Eight weeks after the final therapy session, they will engage in an initial follow-up assessment (T4).

Finally, every family will complete a follow-up survey (T5) 6 months after T4.

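### Active harms inquiry stops outside therapy sessions and its length depends on response at T3, so raw whole-study adverse event counts would be incomplete and could favour the arm with more responders

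*Protocol article*

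**What the plan says.** The Harms section of the protocol article describes one active and one passive route. The active route is "During each therapy session, therapists will inquire about potential adverse events". The passive route is that "participants will be encouraged to report any unexpected effects at any time during the study". Review is by the principal investigator: "All reported adverse events will be discussed with the PI in the regularly held supervision meetings". The only supervision schedule given, in the Adherence section, is itself counted in sessions: "a supervision session with the PI will be scheduled for every fourth therapy session".

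The Participant timeline section sets out when sessions take place. Screening is followed by "a baseline phase that does not include any sessions with the study staff or therapist", during which patients already observe themselves with the app or on paper. Both this section and the Trial design section put that phase after randomisation. Everyone then has two treatment phases of eight patient sessions each, up to T3. Patients who are non-responders at T3 on the YSR Internalizing scale have a third phase before T4. Responders have no further sessions and are assessed at T4, eight weeks after their last one. The article says of responders that they "will conclude their participation in the study" at T3, yet it schedules T4 and T5 for them. The Trial design section says: "A subsequent follow-up evaluation (T5) for all patients will be scheduled 6 months after T4".

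**The concern.** Active ascertainment follows the session calendar, and the trial has long periods without sessions. One of them is the first exposure to the randomised tool. The others follow the end of therapy. In these periods an event is recorded only if the family reports it or, for baseline, if it is recalled at a later session. The passive route is also less clear than it should be for responders: it runs for the duration of the study, and the article says both that their participation ends at T3 and that they are assessed twice more.

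The number of inquiries also depends on a post-randomisation outcome. Self-rated internalizing symptoms at T3 decide who gets eight more sessions, and the trial hypothesises that the app reduces those symptoms more. If that is true, app patients will on average be asked less often, and a raw count over the whole study would lean towards the app without any true difference in safety.

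This matters because the Background says that adolescents with these disorders "have a higher risk of suicidality", and because the article argues that new apps need scientific evaluation if they are to be used safely.

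**Working it through.** **Inputs from the article**
- Introductory therapist sessions: 3 (Participant timeline).
- Patient sessions per treatment phase: 8. Phases: 2 for responders, 3 for non-responders (Trial design, Participant timeline).
- Session frequency: weekly (Intervention description).
- T4: 8 weeks after the last session for responders, at the end of the third phase for non-responders. T5: 6 months after T4 for all.

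**Assumptions**
- 6 months = 26 weeks, and assessments add no time.
- Response rates by arm are not given, so a range is used.
- The length of the baseline phase is not given, so it is left out of the week counts.

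**Reproducing the plan's own figure.** Therapist visits are 3 + 2 × 8 = 19 for responders and 3 + 3 × 8 = 27 for non-responders. Both match the Participant timeline section. From T1 onwards the planned inquiries are 16 and 24.

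**Time under active inquiry, T1 to T5**
- Responders: 16 + 8 + 26 = 50 weeks, of which 16 have sessions (16/50 = 32%). Weeks without: 8 + 26 = 34.
- Non-responders: 24 + 26 = 50 weeks, of which 24 have sessions (24/50 = 48%). Weeks without: 26.
- The baseline phase is additional and has no sessions for anyone.

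**Mean planned inquiries per patient by arm.** With non-response rate q, the mean is 16 + 8q from T1, or 19 + 8q if the introductory sessions are counted. The Trial design and Participant timeline sections disagree on whether those three sessions come before or after randomisation, so both versions are shown.

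| Responders, app vs control (assumed) | From T1: app vs control | Ratio | With introductory sessions | Ratio |
|---|---|---|---|---|
| 50% vs 50% | 20.0 vs 20.0 | 1.00 | 23.0 vs 23.0 | 1.00 |
| 60% vs 40% | 19.2 vs 20.8 | 0.92 | 22.2 vs 23.8 | 0.93 |
| 70% vs 30% | 18.4 vs 21.6 | 0.85 | 21.4 vs 24.6 | 0.87 |

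**Common window.** From T1 to T3 every patient has 16 planned inquiries whatever the response, so the ratio is 16/16 = 1.00 apart from dropout.

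**Choice of denominator.** Both pathways last 50 weeks from T1 to T5. Dividing session-based counts by total follow-up time would therefore leave the ratios above unchanged. Only a denominator of sessions, or of time under active inquiry, removes the imbalance.

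**The case against.** The strongest reply is that the harms scheme is the same in both arms. The gaps at baseline and after therapy apply to both, the T1 to T3 window is balanced by design, and the article describes no between-arm analysis of adverse events that could be biased. All of this stands. A reader might infer that adverse event counts are not comparable between the arms. The article does not support that, because imbalance arises only if response or dropout differs by arm.

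A reader might also take the ratios of 0.92 or 0.85 as 8% or 15% fewer recorded events. That goes too far. The response rates are assumed. Non-responders are asked more often partly because they are treated for eight more weeks, at the same rate of one inquiry per session. Spontaneous reports from responders would also narrow the gap.

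Nor are events outside sessions simply lost. Spontaneous reporting is encouraged throughout, and the first treatment session can pick up baseline events, although no recall period is stated. Patients and caregivers complete the Internalizing scales at every assessment, and the life-event list at T5 touches on illness and accidents. These measures detect worsening or record events, but they are not described as adverse event collection.

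Finally, this is a journal article. The full protocol and the T4 and T5 questionnaires are not shown and may hold harms items. That limits the point to what the article itself fixes: a session-based inquiry whose length depends on response, and wording that leaves the end of responders' participation unclear.

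**Conclusion.** The point holds in a limited form. As described, active harms inquiry is tied to sessions and is absent from the baseline phase and from follow-up after the last session: 34 weeks for responders and 26 for non-responders, with 6 months taken as 26 weeks. Capture in those periods is weaker, not absent. Raw whole-study counts would be incomplete and, because the extra sessions depend on response at T3, could favour the arm with more responders. The size of any imbalance cannot be known from the article: the ratio of mean inquiries is 1.00 if response is equal, and about 0.92 (0.93 with introductory sessions) at an assumed 60% versus 40%. The direction towards the app follows only if the trial's own symptom hypothesis is true. Comparison over T1 to T3 is sound in number of planned inquiries. The change is worth making because it is cheap and replaces an outcome-dependent schedule with a fixed one.

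**What to change.** 1. Add the same short adverse event item set to the patient and caregiver online questionnaires already scheduled at T1, T2, T3, T4 and T5. Each set should cover the time since the previous assessment, with the T1 set reaching back to randomisation.
2. State that harms collection runs from randomisation to T5 for all patients, and how reports arising when no supervision session is due reach the principal investigator.
3. Reconcile the statement that responders' participation ends at T3 with the T4 and T5 assessments given for them in the Trial design and Participant timeline sections.
4. Compare adverse events between arms primarily over the common window to T3. Show later events separately, or per unit of time under active inquiry, so that the additional session inquiries of non-responders do not enter the main comparison.

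The cost is a short amendment, slightly longer questionnaires and more non-serious events to process. Recruitment began in October 2023, so earlier participants will already be past some time points. Their data will lack the new items, and the report should say so.

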## Discussion

The JAY trial aims to examine the effects of a newly developed psychotherapy app, used as an adjunct to a CBT treatment, on THA and therapy outcomes in 13–17-year-old adolescents with internalizing disorders. Effects on internalizing and comorbid symptoms as well as individually defined problems, quality of life, self-perception, emotion regulation strategies, and treatment satisfaction will be analyzed.

Previous research has mainly examined adult samples and has predominantly explored apps as substitutes for psychotherapy instead of CBT-adjacent apps. Moreover, effects of apps on THA have rarely been investigated. As such, this study will address a critical gap in the current knowledge regarding digital interventions for youth and their effects on THA, which might serve as a mediator of the effects on treatment outcomes when compared to traditional paper-and-pencil methods.

Several potential challenges that may arise during the JAY trial must be acknowledged. First, although it has already been discussed that most adolescents in Germany have their own smartphones [44] and the present-day youth is accustomed to living in an increasingly digital environment [43], technological barriers may arise. Some participants might not have a personal (smart-)phone or may be unfamiliar with the use of mobile applications. In the case of the former, loaner devices will be provided. These allow the mere use of the JAY app, and all other functionalities will be locked. Participants will receive an introductory session, in which the use of the app is explained. Staff members will be available for support if technological questions arise during therapy.

The app should be acceptable and user-friendly for adolescents, as otherwise, it could lead to low adherence, frustration, and disengagement among participants. In a smaller pilot study, the app was deployed in therapy sessions with adolescents and their therapists. In qualitative interviews, both parties reported that the app was user-friendly, intuitive, and appropriate for its purpose. It was noted that the introduction of a smartphone app altered the dynamics of the therapist-patient relationship, and patients perceived the app as a replacement for human interaction. This led patients to feel less connected to and supported by their therapist, and adherence to the therapy and the research protocol decreased. To overcome this problem, three sessions with the therapist were integrated into the study design, which precede the baseline phase and focus on building the foundation for a strong therapist-patient relationship and psychoeducation about the complementary role and benefits of the app.

Another important aspect to be considered is data privacy. To prevent a threat to confidentiality, apps should not make patients’ data available to third parties, and the transfer of data to the therapist should only take place with the patient’s informed consent [50, 56]. For this reason, participants will have full control over their data, which will be stored locally on their smartphones. Participants will decide themselves which data to share by uploading them to a secure research server.

Further methodological challenges include a potential bias due to the inability to blind patients and therapists to the interventions. In addition, the unblinded clinician responsible for the outcome assessment during the clinical interviews may also serve as the treating therapists, which could increase the risk of assessment bias. Participants will not be informed about the study hypotheses. Nevertheless, the information they receive may lead them to perceive the JAY app as innovative and anticipate higher adherence to therapy homework. Similarly, therapists may introduce bias when evaluating the therapy homework. In future studies, it is important to consider incorporating independent blinded evaluation of therapy homework adherence into the study design in order to mitigate potential biases.

A final aspect to consider concerns the highly effective nature of the control condition [49], which might make it difficult to identify the incremental effect of the app. It is possible that a larger sample will be required to detect significant differences.

Nonetheless, the JAY trial is expected to provide valuable insights into the applicability of a smartphone app used as an adjunct to CBT-based psychotherapy for youth, and into its impact on adherence to therapy homework between sessions. The app’s utility in supporting diagnostics and intervention will be evaluated, as well as its effect on various outcome measures. The results of this study will contribute to preparing research in the growing field of CBT app development and provide a scientific basis for the use of such apps in psychotherapy with adolescents.

Therefore, the findings of this study are expected to also have an impact on clinical practice and on the extension of treatment options for relevant mental disorders such as anxiety and depressive disorders.

### Public or patient involvement

The protocol was written based on the study design of [name]. There was no public or patient involvement in the planning of the trial or in the process of writing this study protocol.

### Trial status

Issue date: 08.08.2024.

Protocol amendment number: 03.

Authors: [name], MD.

The recruitment for the JAY trial has started in October 2023 and is still ongoing at the time of submission of this protocol. The completion of recruitment is planned for March 2026.

## Data Availability

After the results are published, the final datasets can be obtained from the principal investigator ([name]). The results of the study, especially regarding the primary outcome, will be submitted for publication in relevant journals. Furthermore, patients and their families will have access to the results if they wish. The results will also be presented at internal meetings and workshops as well as at relevant scientific congresses.

## Abbreviations

AUTHARK: App-augmented therapeutic treatment for children with aggressive behaviors
CBCL/6-18R: German version of the Revised Child Behavior Checklist for ages 6–18
CBT: Cognitive behavioral therapy
CEKIP: Center for Child and Adolescent Cognitive Behavior Therapy
CFT 20-R: German version of the Culture Fair Intelligence Test
DISYPS-III: Diagnostic System for Mental Disorders in Children and Adolescents
DISYPS-ILF: The comprehensive Structured Interview for Children and Adolescents according to ICD-10 and DSM-5 from the DISYPS Systems
DRKS: Deutsches Register Klinischer Studien (German Clinical Trials Register)
EMA: Ecological momentary assessment
FEEL-KJ: Modified version of the Questionnaire to Assess Children’s and Adolescents’ Emotion Regulation Strategies
ICC: Intraclass correlation coefficient
ICD-10: International Statistical Classification of Diseases and Related Health Problems, 10th revision
IPL: Individual problem list
ITT: Intention to treat
JAY: Journaling App for Youth
KINDL^R^: Revised Questionnaire for Health-Related Quality of Life Assessment in Children
PI: Principal investigator
RCT: Randomized controlled trial
THA: Therapy homework adherence
SCL-AD-P: Parent (or caregiver)-report Symptom Checklist for Anxiety Symptoms from the DISYPS-III
SCL-AD-S: Self-report Symptom Checklist for Anxiety Symptoms from the DISYPS-III
SCL-DEP-P: Parent (or caregiver)-report Symptom Checklist for Depressive Symptoms from the DISYPS-III
SCL-DEP-S: Self-report Symptom Checklist for Depressive Symptoms from the DISYPS-III
SUS: Modified German version of the System Usability Scale
YSR/11-18R: German version of the Revised Youth Self-Report for ages 11–18
ZUF-8-M: Modified version of the self-report Client Satisfaction Questionnaire
